# Evaluating the feasibility and preliminary efficacy of a Cognitive Occupation-Based programme for people with Multiple Sclerosis (COB-MS): protocol for a feasibility cluster-randomised controlled trial

**DOI:** 10.1186/s13063-020-4179-5

**Published:** 2020-03-17

**Keywords:** Multiple sclerosis, Occupational therapy, Cognitive occupation-based programme, Cognitive rehabilitation, Feasibility, Protocol

## Abstract

**Background:**

Cognitive difficulties experienced by people with multiple sclerosis (MS) impact their quality of life and daily functioning, from childcare and work, to social and self-care activities. Despite the high prevalence of cognitive difficulties seen in MS, there is a lack of developed programmes that target cognition, while also supporting patients by helping them to function well in everyday life. The Cognitive Occupation-Based programme for people with MS (COB-MS) was developed as a holistic, individualised cognitive rehabilitation intervention. It addresses the wide-ranging symptoms and functional difficulties that present in MS, including the ability to maintain employment, social activities, home management and self-care. The aim of the current research is to evaluate the feasibility and preliminary efficacy of COB-MS for people with MS. The focus is on feasibility outcomes as well as functioning associated with cognitive difficulty and secondary outcomes related to cognition, fatigue and quality of life.

**Methods:**

One hundred and twenty people with MS will be assigned to participate in either the COB-MS programme or a treatment as usual, wait-list control group as part of this single-blind, cluster-randomised controlled feasibility and preliminary efficacy trial of the COB-MS programme. The COB-MS group will participate in an eight-session occupational-based cognitive rehabilitation programme over 9 weeks. The primary outcome measure is the goal attainment scaling at 12 weeks. Participants will be assessed pre-intervention, post-intervention and at 12 weeks post-intervention and 6 months post-intervention. Qualitative evaluations of participants’ perspectives will also be examined as part of the feasibility study.

**Discussion:**

Results will provide recommendations for a future definitive trial of COB-MS, with respect to both feasibility and preliminary, clinical efficacy. In the event that results indicate efficacy, study findings will suggest that COB-MS requires consideration as a means of enhancing cognitive and daily functioning in people living with MS.

**Trial registration:**

ISRCTN: ISRCTN11462710. Registered on 9 September 2019.

## Background

Approximately 40–65% of people living with multiple sclerosis (MS) have difficulties with cognition [1–3]. With an average onset age of 30 years [4] and an unpredictable course (e.g. with respect to development and typology; see [5]), MS and its associated cognitive difficulties can have wide-ranging impacts on quality of life and daily functioning in equally wide-ranging occupations, from childcare and work, to social and self-care activities. Research has found that 90% of the estimated 9000 people in Ireland living with MS are of working age [6] and that both fatigue and cognitive difficulties in MS are associated with an increased likelihood of being unemployed [7]. Cognitive difficulties associated with MS typically affect the domains of information processing [8, 9]; memory [10], including working memory impairments [11]; attention (divided and sustained) [12]; new learning [13]; problem-solving [14]; and language (verbal fluency and naming) [15, 16]. The existence of such heterogeneous cognitive difficulties suggests that an individualised approach to rehabilitation may suit this population best. Furthermore, in order to address the needs of people with MS who are not working, there should be access to interventions that support people in working and living independently [6]. Despite the high prevalence of cognitive problems experienced by people with MS, very little has been done to address these difficulties and, more importantly, the impact that they have on a person’s everyday life.

Cognitive abilities have been shown to correlate with other symptoms and functional difficulties that present in MS, including fatigue and depression, as well as the ability to maintain employment, social activities, managing the home and self-care [17–20]. These difficulties impact all aspects of life and clearly suggest an urgent need for a targeted approach to cognitive rehabilitation intervention. A recent, small-scale study [21], with similar aims and objectives, examined the efficacy of a cognitive occupation-based programme for people with MS (COB-MS) via pre-/post-test design. Results from 12 participants revealed significant improvements in relation to goal attainment, memory and attention—indicating a need for further research. Subsequent qualitative research on COB-MS revealed that the COB-MS intervention was perceived as useful and feasible; specifically, people with MS reported that the programme was a validating intervention, and occupational therapists noted its client-centred nature [22]. Similarly, a recent meta-synthesis of qualitative studies, examining the perspectives of people with MS towards cognitive rehabilitation, found that participation in such rehabilitation facilitated reflection and awareness of cognitive deficits; enhanced understanding of MS; provided emotional and social improvements; increased cognitive strategy use; and enhanced confidence, perseverance and optimism [23]. However, to date, there remains a paucity of evidence, as few methodologically rigorous research programmes have been developed to reduce impairment in cognition, decrease the detrimental effects of impairment and support patients by helping them to function well in everyday life [24–26].

COB-MS was developed to provide holistic cognitive rehabilitation in MS [22]. COB-MS focuses on rehabilitation through an individualised cognitive intervention, measured by and taught through an occupational participation perspective. That is, participants have access to a non-pharmacological treatment for cognition that focuses on the aspects of their own daily life that are important to them.

## Aims and objectives

The aim of the current research is to evaluate the feasibility and preliminary efficacy of COB-MS on cognitive and daily functioning for people with MS. Specifically, this study’s objectives are to:Assess the integrity of the protocol and field test the outcome measures and procedures used in the trialDetermine the preliminary efficacy of COB-MS in comparison with treatment as usualDetermine the acceptability of COB-MS and investigate the barriers and facilitators to using COB-MSDetermine the appropriateness of progression to a definitive trial.

## Methods

### Design

The current study is a single-blind, cluster-randomised controlled feasibility trial of COB-MS (see “Interventions”). The structure is based on the Medical Research Council’s (MRC’s) “Framework for development and evaluation of RCTs for complex interventions to improve health” [27]. This study will use a treatment as usual, wait-list control group design and a pre-post study design with two additional follow-up testing times: 12 weeks and 6 months follow-up (i.e. four data points). Follow-up data will be collected to evaluate the sustainability of intervention gains, if evident, as well as to gather data on retention over the entire duration of the trial. Fidelity and qualitative data will also be collected to inform the feasibility assessment of this trial.

### Participants

#### Setting

This trial is a community-based research study that will run COB-MS groups at various locations across the Republic of Ireland. Participants’ own homes and accessible community venues will be used as locations to run the intervention and collect data. The main study site is at the National University of Ireland (NUI) Galway; but data will be collected nationwide, dependent on the location of the participants.

#### Sample size

As this is a feasibility study, a formal sample size calculation to evaluate the clinical effectiveness of COB-MS is not required. Instead, a pragmatic approach is adopted. It is aimed at examining the rate of retention of participants during the intervention and follow-up periods and is based on an average recruitment rate for National Institute for Health Research [28]-funded randomised controlled trials (RCTs). A 9% attrition rate is likely to occur [26]; therefore, if this were an individually randomised trial (at the patient level), a sample of 90 participants would allow for estimation of a retention rate of 91% with a 95% confidence interval (CI) of width equal to 13%. After allowing for clustering, assuming 8 participants per cluster (occupational therapist) and an intracluster correlation coefficient (ICC) = 0.05, the sample size becomes 90 × [1 + (8–1) × 0.05] = 121. Thus, the number of occupational therapists needed is 121/8 = 15. A final sample size of 15 × 8 = 120 people with MS is deemed large enough to provide information regarding the practicalities of a potential definitive randomised trial. This follows Consolidated Standards of Reporting Trials (CONSORT) guidelines for sample size calculation in feasibility studies. See Fig. 1 for the CONSORT flowchart of study participants.

**Fig. 1 Fig1:**
[figure not shown]
COB-MS CONSORT flowchart of study participants

#### Gender issues

A number of different gender issues are relevant to this trial because of the condition (MS) under study, including the ratio of prevalence, age of onset, disease progression, ability to cope and quality of life issues. Data on gender will be collected and will be accounted for in analysis. Statistics, tables, figures and descriptions will focus on relevant gender differences that came up in the course of the project. Findings from this analysis will be included in the final publication. As qualitative data are being collected, the specific impact of the intervention on both male and female participants can be explored in depth. Interviews will allow participants to discuss aspects that are of importance to their own lives, which may or may not be specific to gender. Recruitment will not be gender-balanced, as this is not reflective of the population demographic. Groups (control/intervention) will be balanced, and a representative population will be recruited, if possible.

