#### Secondary outcomes

Various tests and measures are used to evaluate the secondary outcomes. They are listed as follows:*Symbol Digit Modalities Test (SDMT)* [34]. Within the *Minimal Assessment of Cognitive Function in Multiple Sclerosis (MACFIMS)* [35], the SDMT appears to be the strongest predictor of future cognitive decline, thus supporting its sensitivity and construct validity [36]. Similarly, a meta-analysis [37] found the SDMT to have the strongest correlation (*r* = 0.71) with several assessments of processing speed. Research has shown excellent test-retest reliability (*r* = 0.97) at 2-week [38] and 4-week [39] retest intervals for individuals with MS.*California Verbal Learning Test II (CVLT-II)* [40]. The CVLT-II is part of the MACFIMS [35], an established battery of assessments on the fundamental domains of cognition to be assessed in MS. The inter-rater reliability of the CVLT-II ranges from 0.80 to 0.96 [40]. Correlation coefficients for the CVLT-II and CVLT in recall and learning variables range from 0.72 to 0.80, supporting its construct validity [40].*Trail Making Test (TMT)* [41]. The TMT has excellent construct validity, with correlation coefficients ranging from 0.73 to 0.90 with other measures such as the Wechsler Adult Intelligence Scale – III [42, 43]. Inter-rater reliability for the TMT is also high, *r* = 0.96 [44].*Brief Visuospatial Memory Test-Revised (BVMT-R)* [45]. Similar to the CVLT-II, the BVMT-R is part of the MACFIMS. The inter-rater reliability of the BVMT-R ranges from 0.96 to 0.97, and test-retest reliability coefficients range from 0.60 to 0.84 [45].*Everyday Memory Questionnaire-Revised (EMQ-R)* [46]. Research by the authors revealed a Cronbach’s alpha of 0.91 for the EMQ, showing good internal reliability. Strong discriminatory properties were also evident between the neurological and control groups. The researchers then examined the correlations between the EMQ and the EMQ-R, and found that both measures were highly correlated (MS *r* = 0.98; stroke *r* = 0.94; healthy control *r* = 0.97), supporting the EMQ-R as a reliable and valid measure for use in a population of MS.*Everyday Memory Questionnaire Revised-Relative* [46]. Participants will be given the option of having a family member complete the EMQ-R to provide a proxy rating of function and potential change. This was added as an optional measure based on public and patient consultation.*Generalised Self-Efficacy Scale (GSES)* [47]. The GSES aims to predict participants’ ability to cope with daily difficulties and adaptation to any stressful life events [48]. Cronbach’s alphas ranged from .76 to .90 across 23 countries, with the majority in the high .80s.*Modified Fatigue Impact Scale* [49]. This scale is a self-report measure of the impact of fatigue on the participant’s life. It examines physical, cognitive and psychosocial impacts of fatigue. It has a Cronbach’s alpha of .81 and discriminates between fatigue seen in MS and that seen in other conditions.*Multiple Sclerosis Quality of Life-54* [50]. This instrument measures health-related quality of life via 54 generic MS-specific items. It has population-based normative data available and both good internal validity and test-retest reliability.*General Health Questionnaire-12 (GHQ-12)* [51]. The GHQ-12 is a well-validated and standardised 12-item measure of general levels of distress, which can utilise a 4-point Likert score, with higher scores on the scale indicating higher distress. The GHQ is among the most treatment-responsive measures of psychological distress in MS [52, 53].

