#### Demographic and clinical information

Participants will be asked to provide details regarding their age, gender, nationality, residence, education and health, as well as occupational and marital status. These details will be used for the purposes of correlational analysis and interpretation of the clinical data. Furthermore, programme attendance (i.e. 0–8) and home-based review activity completion (i.e. 0–7) will be assessed to examine programme adherence and engagement. Moreover, acceptability of measures will be rated by participants, and rates of recruitment, consent and retention will also be analysed and evaluated.

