### Statistical analysis

Data analysis and reporting will follow 2010 CONSORT guidelines. The feasibility outcomes, recruitment rate, acceptability of COB-MS, rate of unblinding, retention rate and randomisation methods will be reported descriptively and narratively. Analysis will take place once all data have been collected. Means and standard deviations (or medians and interquartile range [IQR] as appropriate) will be used for continuous variables, and counts and percentages for categorical outcomes. The retention rate will be estimated using a 95% confidence interval (CI). Estimates (mean and standard deviations) of the primary outcome variable (i.e. goal attainment scaling), at week 12, will inform sample size calculations of a future definitive trial. Data resulting from primary and secondary outcome measures will be evaluated, per protocol, in terms of preliminary efficacy through a series of 2 (condition) × 4 (time) mixed (multivariate) analyses of variance as well as through correlational analysis. No analysis of health economics or cost-effectiveness will take place in this feasibility study.

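### The gender reporting rule lets the observed data decide which quantitative gender results are emphasised in print

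*Protocol article*

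**What the plan says.** The protocol article's Gender issues section first promises that "Data on gender will be collected and will be accounted for in analysis". It then sets the reporting rule: "Statistics, tables, figures and descriptions will focus on relevant gender differences that came up in the course of the project". The next sentence adds: "Findings from this analysis will be included in the final publication". The section does not say what makes a difference relevant. It also names no outcome, time point, contrast or threshold, and it does not call the analysis exploratory.

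Three other places bear on the point:
- Demographic and clinical information lists gender among the details collected and says: "These details will be used for the purposes of correlational analysis and interpretation of the clinical data".
- Statistical analysis describes the efficacy evaluation as "a series of 2 (condition) × 4 (time) mixed (multivariate) analyses of variance as well as through correlational analysis".
- Dissemination commits to submitting feasibility and efficacy findings whatever they show. It does not mention gender results.

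**The concern.** The rule is stated positively, and it ties emphasis to what was observed. Gender differences that appear are put forward in tables and figures, while those that do not appear get less attention. A reader of the final paper could not tell how many gender comparisons stood behind the ones shown. With many outcomes and several visits, some differences will look notable by chance. Those picked out because they look notable will tend to overstate the true size.

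The Dissemination section takes the opposite approach for feasibility and efficacy results, so the gender rule stands out within the article. An analysis plan that listed gender models would not by itself cancel a published sentence about where reporting will focus.

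**Working it through.** **The plan's own figure.** There is none on this point. The article's only design calculation concerns retention: 90 × [1 + (8 − 1) × 0.05] = 121.5, stated as 121, leading to 15 × 8 = 120 participants. It reproduces, but it has no bearing on gender comparisons.

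**Inputs from the article**
- One primary outcome: "The primary outcome measure is the goal attainment scaling at 12 weeks".
- Ten secondary measures under Secondary outcomes: SDMT, CVLT-II, TMT, BVMT-R, EMQ-R, the relative-completed EMQ-R (optional), GSES, Modified Fatigue Impact Scale, MS Quality of Life-54 and GHQ-12. The total is 11, or 10 without the optional form.
- Four time points (Design).
- 120 participants, 1:1 allocation, so about 60 per arm.

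**Inputs assumed, because the article does not give them**
- Two-sided 5% per test and no true gender effect.
- One to four gender tests per outcome.
- Correlation 0 to 0.5 between outcomes and 0.5 to 0.8 between time points.
- 65–80% women and a within-person correlation of 0.6.

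**Chance of at least one false difference.** For k independent tests it is 1 − 0.95^k:
- k = 10: 40.1%
- k = 11: 43.1%
- k = 22: 67.6%
- k = 33: 81.6%
- k = 44: 89.5%

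For correlated tests, a multivariate-normal simulation (200,000 draws, exchangeable correlation) gives the following.

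| Tests | Outcome correlation 0 | 0.2 | 0.3 | 0.5 |
|---|---|---|---|---|
| 11 (one per outcome) | 43% | 40% | 37% | 30% |
| 22 (two independent per outcome) | 68% | 64% | 61% | 52% |
| 33 (three independent per outcome) | 82% | 79% | 75% | 66% |
| 44 (four visits, time correlation 0.5) | 84% | 82% | 79% | 70% |
| 44 (four visits, time correlation 0.8) | 74% | 70% | 67% | 57% |

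One test per outcome thus gives about 30–43%. For 22 to 44 tests the range is about 52% (22 tests, outcome correlation 0.5) to 90% (44 independent tests).

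**Precision of a gender-by-arm contrast.** Take the change from baseline in SD units. Its variance is 2 × (1 − 0.6) = 0.8. With nF women and nM men per arm, SE = √0.8 × √(2/nF + 2/nM). Clustering is ignored.
- 65% women: nF = 39, nM = 21. SE = 0.894 × √(0.0513 + 0.0952) = 0.342; half-width 1.96 × 0.342 = 0.67 SD.
- 80% women: nF = 48, nM = 12. SE = 0.894 × √(0.0417 + 0.1667) = 0.408; half-width 1.96 × 0.408 = 0.80 SD.

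Under these assumptions a contrast reaches the 5% level only if its estimate is at least about 0.67–0.80 SD. One selected because it looks notable is therefore likely to overstate the truth.

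**The case against.** The strongest reply is that the sentence is being read too hard. It asks for a focus, which is not the same as reporting nothing else, and the sentence after it is not limited to positive findings. It speaks of relevant differences, sets no p-value, and sits in a general statement that goes on to interviews with men and women. Some of what it covers is probably descriptive or qualitative. All of this stands. It means that no publication rate for false differences can be derived from the article itself, and that the planned suppression of null results, which a reader might infer, is not supported.

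Three other stronger readings also fail:
- **Eleven outcomes make a false gender difference likely in two thirds or more of null trials.** They do not. Eleven tests give at most 43%. Two thirds needs ln(1/3)/ln(0.95) = 21.4, that is 22, independent tests, and the article specifies no second family of tests.
- **The lack of a gender term in the condition-by-time model is a defect.** A condensed article may leave model terms to the analysis plan, which is not shown.
- **Gender results will misdirect the definitive trial.** Nothing in the article sends them there. The future sample size rests on goal attainment scaling at week 12 (Statistical analysis). Progression rests on recruitment, protocol adherence, outcomes and a published checklist (Progression criteria).

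What survives is the wording itself. It ties emphasis to what was seen, and the Dissemination promise does not extend to gender.

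**Conclusion.** The point holds as a minor correction against selective emphasis. The article states that quantitative gender reporting will concentrate on differences that emerged, and that these go into the final paper.

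The size is conditional on the assumed 5% level, number of tests and correlations: about 30–43% for one test on each of 11 outcomes, and about 52–90% for 22 to 44 tests. Even the lowest figure is six times the nominal 5%. The imprecision figure rests on the assumed share of women and within-person correlation. None of these rates is a property of the document, and the finding does not depend on any one of them. It depends on the direction of the rule, which favours differences that appeared over those that did not.

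**What to change.** Replace the sentence on where gender reporting will focus with wording such as: *For the primary outcome and for each secondary outcome, the gender-by-arm difference at the 12-week follow-up will be reported with its 95% CI, whether or not a difference is seen. These quantitative gender analyses are exploratory.* Leave the qualitative exploration of gender as it is.

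The cost is one sentence and one supplementary table, from data already collected. The intervals will be wide. With 11 of them there is still about a 30–43% chance under the null that at least one excludes zero. The change does not remove that chance, but it puts every contrast in view so that a single striking one can be read against the rest.

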#### Recruitment

Occupational therapists will be recruited through professional body email (e.g. the Association of Occupational Therapists of Ireland) and through notification on the MS Ireland website, health professionals’ email list and the bi-annual *MS Ireland* research e-zine. The use of snowball sampling will follow, in which occupational therapists may inform other potentially interested occupational therapists of the trial. People with MS will be recruited through trial advertisement in relevant newsletters (e.g. the monthly *MS Ireland* newsletter), on websites offering information and services to people living with MS (e.g. MS Ireland), via recruited occupational therapists as well as through posters and information leaflets posted in relevant clinics (e.g. neurology, general practitioner, primary care clinics, physiotherapy) around the Republic of Ireland. Advertisements will also be posted in any relevant publications, radio, discussion boards and fora, as well as through social media. All individuals interested in participating will self-select through contacting the researchers by phone or email. Informed consent will be obtained and eligibility assessed prior to participation.

